#### Quality of life

The Spanish validated translation (20) of the MSQoL-54 (19) is a self-administered questionnaire with a completion time of approximately 15 min and a Cronbach alpha ranging 0.75–0.96 for the different scales. It consists of 54 items, of which 36 correspond to the generic Short Form-36 Health Survey questionnaire and 18 are specific to MS. 52 items are classified in 12 dimensions. The remaining two individual items measure changes in health status (comparing current health and health during the previous year) and satisfaction with sexual function. In addition to the scores of the dimensions and individual items, two composite scores corresponding to mental and physical health subscales are obtained. The MSQoL-54 questionnaire is widely used and is, therefore, a relevant tool for assessing the impact of the EPPC-MS on participants’ QoL.

#### Emotional impact

The HADS (16) and the Spanish version elaborated by Herrero in 2003 (23) specifically assess the level of anxiety or depression of an individual in the last 7 days. Several studies have validated the translated version in the Spanish population, yielding Cronbach alphas of 0.87–0.90 (24). It consists of a 14-item self-administered questionnaire, including an anxiety and a depression subscales, with seven items each. For each subscale, the scores range from 0 to 3 (0 being the minimum affectation and 3 the maximum) for each item, whereby a 0–7 score indicates no disorder, 8–10 is a questionable case, and a score ≥ 11 indicates the presence of anxiety or depressive disorder. HADS is a useful tool for detecting individuals with a neuropsychological condition requiring referral to a specialist for assessment and care (exclusion criteria) and evaluating the program’s effectiveness on MS-related emotional impact.

#### Fatigue

The FSS (21) and its Spanish translation by Tola in 1998 (25) is a 9-item self-administered questionnaire, rated on a 1–7 scale (1 being “strongly agree” and 7, “strongly disagree”) assessing the impact of fatigue on a person’s daily life. The Cronbach alpha was 0.81 for its English version. This tool will enable the evaluation of the program’s impact on fatigue self-management.

#### Patient activation (engagement)

The PAM-13 and its validated Spanish version by Moreno-Chico in 2017 (22) is an instrument assessing knowledge, skills and people’s confidence in self-management of their health and medical care. The validation of the Spanish version showed an Item Separation Index (i.e., comparable to Cronbach alpha, whereby values ≥0.7 show a differentiated scale between individuals and items along the latent trait) of 6.64 (22). PAM-13 consists of a self-administered questionnaire of 13 items, rated on a 1–4 scale (1 being “strongly agree” and 4 being “strongly disagree”). PAM-13 is a useful tool to assess patients’ confidence regarding disease self-management and will enable evaluating the program’s impact on the activation and involvement of participants.

#### Knowledge of MS

Given the lack of validated questionnaires in Spanish assessing MS-related knowledge, the expert panel of the EPPC developed a specific questionnaire to assess MS-related knowledge. This questionnaire assesses disease-related knowledge and specific aspects essential to empower MS patients identified as the target population through a qualitative study of focus groups (12). This questionnaire, which has not been validated yet, was designed based on the previous pilot qualitative study (12) and will assess the impact of the program on the acquired knowledge.

#### Habits and lifestyles

The EPPC coordinating panel developed an MS-specific questionnaire to assess habits and lifestyles. This questionnaire awaits validation, but has already been used in other program variants, demonstrating its usefulness in assessing changes due to participation in this program (4, 26).

#### Participant-reported experience and expert patient-reported experience

The EPPC coordinating panel developed a specific questionnaire to assess satisfaction related to their participation and experience with the intervention. This questionnaire has already been used in other variants of the program, demonstrating its usefulness in assessing participants’ experience in this program (4, 17, 26).

### Data management

Study data will be collected and managed using REDCap electronic data capture tools hosted at Vall d’Hebron Research Institute (VHIR). The REDCap (Research Electronic Data Capture) is a secure, web-based software platform designed to support data capture fro research studies. The REDCap provides (1) an intuitive interface for validated data capture; (2) audit trail for tracking data manipulation and export procedures; (3) automated export procedures for seamless data downloads to common statistical packages; and (4) procedures for data integration and interoperability with external sources (27, 28). Each participant will be assigned a code for de-identification. No data will be shared. Each site will send the results to the coordinating center, and the PI will be responsible for guarding the database, which will be saved until the analysis is complete.

### Contact details of participants

Each unit will provide minimum and essential contact details to allow communication between the program coordinating team and EP or participant candidates. Data will be stored by the coordinating team in a different database than the study’s database, and will be destroyed after the intervention is completed. Only the PIs at each participating unit will have access to the database. These data must include the code assigned to each individual, name and surname, telephone number, and e-mail address to send them the program questionnaires and instructions to connect to the Patient Expert Catalonia Program platform.

### Variables and questionnaires

The REDCap is an electronic data capture software and workflow methodology we will use to design the research database (27, 28). REDCap, developed by Vanderbilt University, provides institutional licenses to various clinical research institutes worldwide. In this study, the Basic Statistics Unit (UBE) associated with the Vall d’Hebron Research Institute (VHIR) of the Vall d’Hebron Barcelona Hospital Campus will manage the institutional license provided and guarantee security of the data and the computer support for databases created with this system. Specifically, in this study, the UBE will support the study’s PI to create the database and, through a collaboration agreement, will perform the statistical analysis of this study’s outcomes. The coordinating team will enter all data related to the questionnaires into the study database using REDCap as participants complete the questionnaires. The centers’ research teams will provide all clinical or disease-related variables with a code for each participant, without any sensitive data allowing the identification of study participants. Therefore, their identity will remain blind to the research team of each center, who will have access to the REDCap platform for data entry. As mentioned above, each center will send the results to the coordinating center through the platform. The nurse principal investigator will keep the database and save it until the end of the analysis related to the research project.

### Statistical analysis

Statistical analyses will be performed on the intention-to-treat (ITT) population, defined as the population of patients starting the intervention, irrespective of program completion. Continuous variables will be described as mean and standard deviation (SD) or, in case of non-compliance with normality criteria, median and interquartile range (IQR), and categorical variables as absolute frequency and percentages. The non-parametric U Mann–Whitney test for independent samples and the Wilcoxon test for dependent samples will be used to analyze the relationship between a categorical variable and a continuous variable. The Chi-squared test or the Fisher’s exact test will be used to analyze the relationship between two categorical variables. For the secondary outcomes, changes in the study variables throughout time (i.e., before and after the intervention) will be analyzed using an ANCOVA or linear mixed model to etimate changes in effect size. No methods to handle missing data (i.e., imputation) will be applied. A significance level of 5% will be considered. Data will be analyzed using the latest version of the Statistical Package for the Social Sciences (SPSS) software (IBM, Armonk, New York, United States).

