## Objectives

The primary objective of this study is to deploy the EPPC-MS across Catalonia. Secondary objectives are to evaluate the effectiveness of the EPPC-MS in reducing the emotional impact of MS and improving QoL, fatigue management, patient activation, habits and lifestyles, and MS knowledge of participants after completing the program. Additional secondary objectives are to evaluate the effectiveness of EPPC-MS in improving health outcomes according to the type of MS, the use of healthcare services by participants, the satisfaction of the EP and the participants with the EPPC-MS, and the long-term persistence of program benefits (at 6 and 12 months).

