Each of the participating teams will select three EP candidates, who will be scheduled for interviews with the PI and the institutional managers of the EPPC to further assess their adequacy to fulfill the EP role. Disease-related knowledge will be assessed using questions from the disease knowledge, habits and lifestyle, and quality of life questionnaires used to evaluate the program, and candidates will be engaged to speak about self-management, self-care, and their future role as EP to assess their predisposition, leadership skills, and communication abilities. This strategy for EP selection has been used previously in other versions of the program (17). Moreover, the interviews will be conducted remotely using the same platform that will be used for the program sessions to confirm the ability of the EP candidates to use it. The PI and EPPC managers will select one EP per team, who will be provided with the session materials and will be trained for their role. The training sessions will allow us to confirm the adequacy of the EPs and, if necessary, the selection may be reconsidered.

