### Sample size

Sample size is estimated based on the deployment of the EPPC-MS across Catalonia (primary outcome). Sample size was calculated by prioritizing those units willing to participate in the study and interested in implementing the program in the future to offer it to the people with MS followed up at the unit regularly. Of the 7 units willing to participate, the 2 units located in the Tarragona area (Tarragona and Reus units) will particpate as joint team, resulting in a total of six participating teams. Each MS team will include two groups of people with MS, of which one group will include people with relapsing MS and the other group people with progressive MS, resulting in a total of 12 groups, with six groups for each MS type. Based on the methodology used in the program, the recruitment target will be 12 people with MS per group (144 individuals in total). We expect this group size will compensate for possible losses during the intervention and ensure a minimum of 8–10 participants per group throughout the program (96–120 participants) (4). We estimated this sample size based on the number of people with MS in Catalonia (⁓10,000) and the number cared for at each of the MS units. Ideally, the exact calculation of the sample size required to assess the study’s secondary outcomes (EPPC-MS effects) should be based on the results of a pilot study testing the program’s effects in a smaller sample of patients. However, this study has not yet been completed. If the 12 groups are insufficient to reach an appropriate sample, the participating investigators will contact the Ethics Committees to request their approval to expand the number of groups.

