### Limitations

Health regulations and recommendations owing to the COVID-19 pandemic may alter the study’s schedule due to the restrictions at the MS units on participants’ attendance to assess inclusion and exclusion criteria. Being a study lasting more than 12 months, the elimination of the knowledge-induced response of studied participants is guaranteed (37). With respect to session attendance and missing data, the program will ensure attendance by sending reminders to confirm it and, if necessary, re-scheduling sessions. Furthermore, the questionnaires’ receipt from each participant will be monitored and reminders will be sent to ensure collection of data at all timepoints. Regarding evaluation instruments, a Spanish version of the BICAMS (15) battery has been developed for the Argentine population (15). To date, we do not have scales for the population of Spain. Nevertheless, the demographic characteristics of the sample used in Vanotti’s study are likely extrapolable to the population’s demographic characteristics in the present study. Likewise, instruments evaluating MS-related knowledge and habits and lifestyle are still missing. Therefore, this study will evaluate these variables using questionnaires developed by the EPPC and awaiting validation. In this regard, an objective instrument to evaluate EPs’ skills and knowledge is missing and therefore, existing differences among EPs may influence this study’s results. However, we believe that EP planned training before starting the learning sessions may partly even any potential differences.

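### The permitted participant-level tests ignore delivery in 12 peer groups by six expert patients; if change is correlated within groups, the 5% level for secondary outcomes is exceeded

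*Protocol article*

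**What the plan says.** The Statistical analysis section names three sets of methods. For a categorical against a continuous variable: "The non-parametric U Mann–Whitney test for independent samples and the Wilcoxon test for dependent samples will be used to analyze the relationship". For categorical data: "The Chi-squared test or the Fisher’s exact test will be used to analyze the relationship between two categorical variables". Changes over time in the secondary outcomes "will be analyzed using an ANCOVA or linear mixed model to etimate changes in effect size". The threshold is common to all: "A significance level of 5% will be considered". No random effect is named, and no group, team or EP term appears in any of these sentences.

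The design is clustered by construction. The Sample size section describes two groups per team, "resulting in a total of 12 groups, with six groups for each MS type". Under Selection of participants and EPs, "The PI and EPPC managers will select one EP per team", so six EPs each serve one relapsing and one progressive group. The Intervention section attributes learning to the EP and to the shared experience of the group. The Limitations section concedes that "existing differences among EPs may influence" the results, and the only remedy it offers is training before the sessions. The Objectives include "improving health outcomes according to the type of MS", a contrast in which type is a property of the whole group.

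**The concern.** People who learn from the same leader and from each other may change in similar ways. A test that counts each of them as a separate piece of evidence then understates the standard error of the mean change. The relapsing-versus-progressive comparison sets six groups against six, so variation between groups enters that contrast directly.

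Deployment, the primary outcome, has no significance test described. The effectiveness outcomes therefore carry whatever statistical inference the study makes, and there is no control arm. Intervals that are too narrow would overstate the evidence for a program that is to be disseminated to other units. A mixed model with a participant effect alone would not remove the problem, because the correlation that matters is in the change itself.

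**Working it through.** **The plan's own figure.** 6 teams × 2 groups × 12 = 144 recruited; 12 × 8 to 12 × 10 = 96–120 retained. Both match the Sample size section. There is no power calculation to reproduce.

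**Inputs.** Group size m = 8–12 and 12 groups (Sample size). Six EPs with 16–24 participants each (one EP per team, two groups per team). Significance level 5% (Statistical analysis); sidedness is not stated and two-sided is assumed. The ICC of change scores is not in the document; 0.01–0.10 is an assumed range.

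**Formulas.** Design effect DE = 1 + (m − 1) × ICC. True over reported standard error = √DE. Actual error rate = 2 × [1 − Φ(1.96/√DE)]. Effective number = N/DE.

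**Example.** m = 12, ICC 0.05: DE = 1 + 11 × 0.05 = 1.55; √1.55 = 1.245; 1.96/1.245 = 1.574; error rate 11.5%; 144/1.55 = 93.

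| ICC (assumed) | DE, m = 8 | Error rate, m = 8 | DE, m = 12 | Error rate, m = 12 | Effective N of 144 |
|---|---|---|---|---|---|
| 0.01 | 1.07 | 5.8% | 1.11 | 6.3% | 130 |
| 0.02 | 1.14 | 6.6% | 1.22 | 7.6% | 118 |
| 0.05 | 1.35 | 9.2% | 1.55 | 11.5% | 93 |
| 0.10 | 1.70 | 13.3% | 2.10 | 17.6% | 69 |

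At ICC 0.05 the true standard error is √1.35 = 1.16 to √1.55 = 1.24 times the reported one, that is 16–24% larger.

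**Simulation check.** 5,000 data sets per scenario with no effect, 12 groups of 12 and correlation at group level:

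| ICC | Wilcoxon on change | Mann–Whitney, 6 v 6 groups |
|---|---|---|
| 0 | 5.4% | 4.9% |
| 0.01 | 6.3% | 6.5% |
| 0.02 | 7.4% | 7.7% |
| 0.05 | 11.4% | 11.5% |
| 0.10 | 16.4% | 16.3% |

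With 10 or 12 per group, t-tests on group means stayed at 4.6–5.5% at every ICC from 0 to 0.10.

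**Correlation only through the EP.** At ICC 0.05, DE = 1 + 15 × 0.05 = 1.75 (16 per EP) to 1 + 23 × 0.05 = 2.15 (24 per EP), giving pre-post error rates of 13.8% to 18.1%. Simulated Wilcoxon rates with 24 per EP were 9.7%, 17.4% and 27.1% at ICC 0.02, 0.05 and 0.10. The Mann–Whitney test by MS type gave 4.6%, 4.6% and 4.1%. The EP effect is common to both types and cancels in the difference, while the unpaired test still counts it as noise.

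**The case against.** The strongest reply is that the rank-test sentence is generic. The effectiveness outcomes have their own sentence, and it already names a linear mixed model that could carry group and EP effects. This is also a journal article: an analysis plan not shown may set the random effects and degrees of freedom, and their absence here is not a fault. Both points stand. A reader might infer that the plan has no suitable method at all, and the text does not support that. What remains is that the section expressly permits ANCOVA as an equal alternative, together with tests that assume independence. Later detail can complete the mixed model, but it cannot make a plain ANCOVA or a standard rank test allow for groups.

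A second reply is that no ICC is given. That also stands. A reader might conclude that the 5% level is certainly lost. It is lost only if change is correlated within groups, and at ICC 0.01–0.02 the excess is modest.

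Third, a reader might take every comparison to be anti-conservative. EP-only correlation makes the MS-type test slightly conservative, so the direction depends on where the correlation sits.

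Finally, the affected outcomes are secondary, the sample was not sized for them, and the Limitations section disclaims a causal aim. This lowers the priority of the point. It does not make the permitted tests valid for this design.

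**Conclusion.** The point holds in conditional form. The section permits participant-level inference in a design with 12 groups and six EPs, and fixes no group or team/EP term. Under positive within-group correlation of change, the pre-post tests and the MS-type comparison are anti-conservative: about 6% at ICC 0.01, 7–8% at 0.02, 9–11.5% at 0.05 and 13–18% at 0.10, for 8–12 per group. Under EP-only correlation the pre-post rate is about 14–18% at ICC 0.05, and the unpaired MS-type test is slightly conservative rather than liberal.

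These figures rest on an assumed ICC, equal group sizes and two-sided testing. The primary outcome, deployment, is not affected. The wording should be corrected, but the study's main conclusion does not depend on it.

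**What to change.** Reword the Statistical analysis section as follows:

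- Inference on change uses the linear mixed model, not ANCOVA.
- Fixed effects are time, MS type and time-by-type, with a random effect for participant.
- Group and team/EP effects both act on the time contrast. A team intercept alone would miss EP differences in change. Team may be fixed, in which case the conclusion refers to these six EPs.
- Degrees of freedom are Satterthwaite or Kenward–Roger.
- If the variance components cannot be estimated with 12 groups and six EPs, fall back to group mean changes, paired within team for the MS-type comparison. For overall change, 12 group means still count an EP's two groups as independent, so six team means (5 degrees of freedom) are the cautious version.
- Report the ICC. Keep the Mann–Whitney, Wilcoxon, chi-squared and Fisher tests for description.

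No new data are needed: group and unit are fixed by the design and noted for each session. The cost is precision. At ICC 0.05 with 12 per group and 11 degrees of freedom, intervals are about 1.245 × 2.20/1.96 = 1.4 times as wide. The paired six-team check has only 5 degrees of freedom (critical t 2.57).

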### Monitoring

A study monitor will visit the participating centers before starting recruitment to ensure that they have the human and material resources and the necessary training for their satisfactory participation in the study and in accordance with the protocol. The research staff of each unit will attend a training session before the recruitment starts and a monthly meeting to verify uniformity in data collection. The role as observer of the study’s nurse PI during the program will facilitate the prompt detection of protocol deviations and data collected in the field notebook will allow the research team to implement the necessary correcting actions. For example, unanswered questions during each group session will be collected in a field notebook by the research team and answered in the next session. Furthermore, inappropriate or inaccurate information shared during sessions will be clarified by the EP in the next session, with the support of the research team.

A data monitoring committee was deemed unnecessary in this study, as the intervention was anticipated to cause no harm to any of the participants. The EPPC has been implemented for other chronic conditions, such as heart failure, chronic obstructive pulmonary disease, Chagas disease, and intestinal inflammatory bowel disease, demonstrating the safety of peer-led educational interventions (17, 26, 29). In this regard, this study will not include a safety assessment, as the intervention is not expected to generate any related adverse events. Nevertheless, changes in the HADS (23) subscales scores may indirectly provide valuable safety information and will be monitored. Furthermore, a negative impact of the intervention may lead to missing sessions, and we will contact participants with missing sessions to provide support. If the investigators detect any issues, the participant will be referred to the relevant specialist.

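### The analysis is called intention-to-treat, but with no missing-data method and the model left open, the before-after results are available-case unless the mixed model is used

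*Protocol article*

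**What the plan says.** In the protocol article, Statistical analysis:

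- The analysis set is the "intention-to-treat (ITT) population, defined as the population of patients starting the intervention, irrespective of program completion".
- On missing data: "No methods to handle missing data (i.e., imputation) will be applied".
- On tests: "The non-parametric U Mann–Whitney test for independent samples and the Wilcoxon test for dependent samples will be used" to relate a categorical variable to a continuous one.
- Changes over time in the secondary outcomes "will be analyzed using an ANCOVA or linear mixed model to etimate changes in effect size". No rule is given for choosing between the two.

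Elsewhere in the article:

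- Sample size: the recruitment target of 12 per group (144 in all) is meant to absorb losses and "ensure a minimum of 8–10 participants per group throughout the program (96–120 participants").
- Monitoring: "a negative impact of the intervention may lead to missing sessions".
- Objectives: effectiveness by type of MS, and persistence of benefit at 6 and 12 months, are both secondary objectives.
- Participant and unit timeline: relapsing and progressive participants are recruited as separate groups, so MS type is an observed characteristic and not a randomised factor.

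**The concern.** The label and the methods do not describe the same people. The set contains everyone who starts. A paired Wilcoxon test, or an ANCOVA of one follow-up visit on baseline, can use only those who supplied both values. A likelihood-based mixed model keeps anyone with at least one value and needs no imputation if data are missing at random. The unresolved choice between ANCOVA and a mixed model therefore decides whether the intention-to-treat claim can hold.

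The study has a single arm, so no control group would share the effect of selective loss. If participants who do badly are also those who stop answering, the mean change among those who remain is too favourable. On either reading of the missing-data sentence, an analysis that assigns values to people without follow-up is ruled out, so the plan has no way of showing how far this matters.

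A second consequence concerns MS type. If the types start at different levels, ANCOVA and a comparison of mean changes answer different questions, and the plan does not say which is wanted.

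**Working it through.** **1. The plan's own figures.** 6 teams × 2 groups × 12 = 144; 12 × 10 = 120; 12 × 8 = 96. These reproduce exactly. The tolerated loss is 1 − 120/144 = 16.7% to 1 − 96/144 = 33.3%. This is a floor on group size during the programme. It is used below only as an assumed range for missing questionnaires.

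**2. Bias of the available-case mean change.** Bias = proportion lost × (mean change in those retained − mean change in those lost). The difference is assumed to be 0.25–0.5 SD of the change; the article gives no figure.

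- Low corner: 0.167 × 0.25 = 0.04 SD. Standard error 1/√120 = 0.091 SD. Ratio 0.042/0.091 = 0.46.
- High corner: 0.333 × 0.5 = 0.17 SD. Standard error 1/√96 = 0.102 SD. Ratio 0.167/0.102 = 1.6.

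**3. Does the model choice matter?** A simulation of 600 runs per setting used 144 participants, four visits, score SD 1, correlation 0.6 between all visits and a true change of zero. Months 6 and 12 were missing for one sixth or one third of participants. All mechanisms are assumed. The estimate is the 12-month change in score SDs; each pair is for 17% and 33% loss.

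- Loss completely at random: available-case and mixed-model estimates both about 0; Wilcoxon rejects in 5% of runs.
- Loss dependent on the observed Week 9 change: available-case +0.08 and +0.16; Wilcoxon rejects in 16% and 40%; mixed model about 0.
- Loss dependent on the 12-month change itself: available-case +0.16 and +0.30; Wilcoxon rejects in 52% and 92%; mixed model +0.08 and +0.15.

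The mixed model removes the bias in the second case and about half of it in the third.

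**4. What a no-benefit sensitivity analysis does.** If participants without post-intervention data are given a mean change of zero, an observed mean change d becomes (retained/144) × d. That is 120/144 = 0.83d or 96/144 = 0.67d over the assumed range.

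**5. MS type.** If both types change equally but differ at baseline, the ANCOVA type effect is the baseline gap × (1 − pre-post correlation). With an assumed gap of 0.5 SD and correlation of 0.7 it is 0.5 × 0.3 = 0.15 SD. Over gaps of 0.3–0.8 SD and correlations of 0.5–0.8 it runs from 0.3 × 0.2 = 0.06 to 0.8 × 0.5 = 0.40 SD. With no gap it is zero.

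**The case against.** The strongest reply is that the plan already allows the right analysis. Its missing-data sentence names imputation, a mixed model needs none, and the two are compatible. A statistics unit will run the analysis, and an article may leave final model details to an analysis plan that is not shown. This stands in part: if the mixed model is used, the absence of imputation is no error. What remains is that the article itself names alternatives that use different people, and puts one intention-to-treat label over all of them.

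Several stronger readings are tempting but not supported:

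- *A third of the outcome data will be missing.* The 96–120 is a minimum attendance figure. Questionnaires go out through the electronic platform, are resent weekly for three weeks and are monitored, so someone who leaves the sessions can still answer. The Intervention section does link collection at 6 and 12 months to the follow-up sessions, so some dependence on attendance is possible.
- *Loss is known to be informative.* The Monitoring section says only that harm may lead to missed sessions, and it plans contact and support. It does not mention questionnaires.
- *The mixed model cures the problem.* It does not when loss depends on unseen outcomes, and it gains little for people with baseline data only, who are the likely losses during the programme.
- *ANCOVA distorts the MS-type comparison.* The article assigns no method to that comparison and reports no baseline gap. ANCOVA estimates the difference at equal baseline, which is a legitimate question; it misleads only if the difference in mean change is what is wanted.

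**Conclusion.** The point holds in a limited form. As written, the before-after effectiveness results are available-case unless the mixed model is the one used, and no sensitivity analysis is foreseen. The possible overstatement is 0.04–0.17 SD of change, about 0.5 to 1.6 standard errors. This rests on two assumptions that the article does not supply: 17–33% of questionnaires missing, and a change 0.25–0.5 SD less favourable in those lost. If loss is unrelated to outcome, the bias is zero. The MS-type shift depends on a baseline gap, for which the article gives no figure. Only secondary outcomes are affected; the primary outcome is deployment. The change is worth making because it is cheap, but the study does not stand or fall by it.

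**What to change.** Change the Statistical analysis section as follows:

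1. Make one linear mixed model the single analysis of the continuous secondary outcomes. Use every available visit (baseline, Week 9, Months 6 and 12) from every participant who starts, with visit as a factor, MS type and their interaction, and with baseline as a response. Remove the ANCOVA alternative.
2. Label any Wilcoxon result as available-case.
3. Replace the sentence that excludes missing-data methods with a statement that the model assumes data missing at random and uses no imputation.
4. Add one sensitivity analysis assuming no benefit in participants without post-intervention data, because the mixed model alone does not remove bias from loss that is not at random.
5. State in advance whether the MS-type comparison targets the difference in mean change or the difference at equal baseline. The model in item 1 gives the former.

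The cost is a few sentences and one extra run, with no change to conduct or data collection. The estimate may turn out less favourable.
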